## Abstract

**Background:**

Enjoyment at work and overall happiness are essential elements of a thriving workforce, particularly in high-pressure environments like healthcare. Nurses frequently experience occupational burnout and stress due to the demanding nature of their profession, which can adversely affect their performance, job satisfaction, and overall well-being. Understanding the factors that contribute to happiness in nursing is crucial, as fostering a positive work environment can lead to improved patient care, reduced turnover rates, and enhanced mental health among healthcare professionals.

**Objective:**

This study aims to systematically investigate the current state of happiness among nurses in order to identify perceived strategies for enhancing their well-being. By employing a mixed-methods approach, we will gather quantitative data on happiness levels and qualitative insights into the experiences and perceptions of nurses regarding their work environment. The ultimate goal is to develop evidence-based recommendations that can be implemented within healthcare settings to promote happiness and mitigate the effects of burnout and stress, thereby contributing to a healthier and more productive workforce.

**Methods:**

Utilizing a mixed-method protocol, the research consists of two distinct phases. The quantitative phase employs a two-stage sampling method to select participants from ten randomly chosen hospitals within a province, ensuring a representative sample. In the qualitative phase, snowball sampling will be utilized to achieve data saturation, allowing for a comprehensive understanding of the factors influencing happiness in nursing. Data collection will involve a range of instruments, including a demographic characteristics and occupational features checklist, the Oxford Happiness Questionnaire, and semi-structured interviews to gather in-depth insights. Data analysis will be conducted using SPSS-24 statistical software for quantitative data and MAXQDA for qualitative data, enabling a robust examination of the findings.

**Result:**

The study is expected to yield a comprehensive understanding of the levels and determinants of happiness among nurses. Quantitative data will provide statistical insights into the prevalence of happiness and its correlation with demographic and occupational factors. Qualitative findings are anticipated to uncover nuanced perspectives on the challenges and enablers of workplace happiness, offering valuable context to the quantitative results. Together, these findings will inform actionable recommendations for fostering a supportive work environment in healthcare settings.

**Conclusions:**

The anticipated outcomes of this study highlight the positive impact of workplace happiness on nurses’ health, job satisfaction, and overall quality of patient care. By identifying actionable perceived strategies to promote happiness in the workplace, this research aims to contribute to the development of supportive environments that enhance both staff well-being and patient outcomes. Ultimately, this study represents a vital step toward fostering a healthier, more engaged nursing workforce.

**Ethics approval:**

IR.MAZUMS.IMAMHOSPITAL.REC.1402.119

## 1. Introduction

### 1.1 Context and challenges

Happiness is often regarded as one of the most profound gifts of human existence. According to numerous experts, all human behaviors are ultimately aimed at achieving this elusive state [1]. Happiness not only serves as a fundamental measure of mental health but also brings a multitude of tangible benefits that extend beyond the individual. Research indicates that happiness can enhance physical health, reduce psychological distress, and even contribute to a longer lifespan. Empirical studies have consistently shown that happy individuals tend to experience a range of positive outcomes, including stronger supportive relationships, improved mental and physical health, and, consequently, increased longevity [2]. In the context of healthcare, the happiness of professionals—especially nurses—is paramount. Nurses are the backbone of the healthcare system, often serving as the primary point of contact for patients. Their well-being directly influences not only their job satisfaction but also the quality of care they provide. A happy nurse is more likely to exhibit compassion, empathy, and resilience, which are critical attributes in a demanding healthcare environment. Conversely, unhappiness among nurses can lead to burnout, decreased job performance, and ultimately impact patient outcomes. Despite the recognized importance of happiness in healthcare settings, many nurses face significant challenges that can hinder their well-being. Factors such as high workloads, emotional strain, and organizational pressures contribute to a stressful work environment. As a result, addressing the happiness of nurses is not merely a matter of individual well-being but a crucial component of fostering a sustainable and effective healthcare system. This underscores the need for targeted interventions aimed at enhancing happiness among nursing professionals, which can lead to improved job satisfaction and better patient care.

### 1.2. Background

Happiness is increasingly recognized as a vital component of health, as emphasized by the World Health Organization [3,4]. In many countries, happiness levels are measured as indicators of quality of life [5]. Ed Diener, a leading researcher in happiness studies, defines happiness as the experience of life satisfaction and enduring joy, with minimal unpleasant emotions such as grief or anger [6]“. It comprises several elements: an emotional component related to cheerful disposition, a social component linked to enjoyment of relationships and social support, and a cognitive component that influences how individuals process information, interpret experiences, and ultimately feel joy and optimism [7].

The World Happiness Report (2017–2019) highlights significant disparities in happiness across nations, with Finland ranking highest and Afghanistan lowest. The Islamic Republic of Iran ranks 118th among 153 countries, indicating a need for improvement, particularly compared to some Eastern Mediterranean countries like Saudi Arabia and Pakistan [8].

Despite the historical quest for happiness [9], research on this concept remains relatively new [10]. Happiness is crucial in all professions, especially nursing, where practitioners face unique challenges. Nurses are in constant contact with patients, requiring them to be compassionate and energetic—qualities closely tied to happiness [11]. However, they also encounter significant stressors, including exposure to patients’ pain, heavy workloads, and job dissatisfaction, which contribute to high levels of burnout [12]. A study conducted in New Zealand in 2020 reported that personal burnout prevalence was 60%, work-related burnout was 55%, and patient-related burnout was 19% [13]. The consequences of occupational stress for nurses include fatigue, lack of empathy, and job burnout [14,15]. These negative effects not only impact individual nurses but also extend to patients and healthcare organizations, leading to poor communication, dissatisfaction, and high staff turnover [15–17]. Despite the historical nature of these issues, the increasing prevalence of burnout suggests a need for innovative solutions.

Numerous studies have attempted to address burnout, yet evidence of successful and sustainable interventions remains limited [18]. The ongoing healthcare crisis has become normalized, necessitating radical transformative approaches to combat burnout [19]. One promising strategy is fostering happiness in the workplace. “Enjoyment in work” and happiness are essential for enabling healthcare professionals to positively impact their work goals and meaning [20,21], potentially serving as antidotes to burnout and stress [22].

As healthcare environments grow increasingly complex, the need for patient-centered, safe, and effective nursing care becomes more critical [21]. Developing healthcare settings that allow nurses to find meaning and enjoyment in their daily work is essential for workforce engagement and retention [21]. Despite the significance of happiness in professional contexts, research specifically addressing happiness among nurses remains limited [23], highlighting the necessity for further exploration into well-being within nursing literature. Addressing this gap, the present protocol responds to a pressing academic problem: while existing literature has extensively documented occupational burnout, stress, and turnover among nurses, there is a lack of positive, strengths-based approaches—specifically, the systematic identification of strategies to promote happiness rather than merely reducing negative states. Current evidence on sustainable interventions to enhance nurse well-being is scarce, with most studies adopting reactive rather than transformative frameworks. This study directly shifts the focus from burnout mitigation to happiness promotion, aligning with global health system priorities such as the Quadruple Aim—improving patient care, enhancing workforce health, reducing costs, and restoring meaning in work. By employing a rigorous mixed-methods design combining the Oxford Happiness Questionnaire and in-depth qualitative interviews, this research will provide statistical insights into the prevalence and correlates of happiness among nurses alongside rich, contextual understandings of their lived experiences. Ultimately, the findings will yield actionable, evidence-based recommendations for healthcare administrators and policymakers, thereby contributing to public health, health policies, and the existing body of knowledge in this vital area.

## 2. Materials and methods

This protocol describes a mixed-methods investigation approved by the Ethics Committee for Health Research Ethics of Mazandaran University of Medical Sciences (approval code: IR.MAZUMS.IMAMHOSPITAL.REC.1402.119). The study consists of two phases. The first phase involves a cross-sectional survey, and the second phase comprises semi-structured interviews. All procedures will be conducted in accordance with the ethical principles outlined in the Declaration of Helsinki and relevant national guidelines. Written informed consent will be obtained from all participants prior to their involvement in any study-related procedures, including both the quantitative survey and qualitative interviews. An overview of the different phases containing aims, methods, and participants are depicted in Table 1.

**Table 1 pone.0354376.t001:** The study overview.

Phases	Aim	Methods	Participants
**Phase 1**			
Quantitative study (Cross-sectional study)	Investigate happiness (Identifying happiness levels and key demographic and occupational variables that contribute to or detract from happiness in the workplace)	Checklist of demographic characteristics and occupational features Oxford Happiness Questionnaire	Nurses
**Phase 2**			
Qualitative study	- Exploring the complex factors influencing nurses’ happiness in their work environment - Identifying strategies to promote happiness	In-depth interviews	Nurses

This manuscript details the protocol for a study that has not yet initiated participant recruitment. The planned timeline for the study is as follows:

Recruitment for both the quantitative (cross-sectional) and qualitative (interview) phases is anticipated to begin in 20 May 2026 and is expected to be completed within 4 months (20 Sep 2026). Data collection is scheduled to run concurrently with recruitment and is projected to be finalized within 3 months (20 Des 2026). Data analysis and compilation of results are planned to be completed within 4 months after the end of data collection.

### 2.1 Study 1: Cross‑sectional survey

This study adopts a sequential explanatory mixed‑methods design. The rationale for this design is that the quantitative phase (cross‑sectional survey) will first identify the levels and correlates of happiness among nurses. Subsequently, the qualitative phase (semi‑structured interviews) will be used to explain, elaborate on, and provide contextual depth to the quantitative findings. This design is well‑suited to our aim of developing evidence‑based, actionable strategies, as the qualitative data will help interpret statistical patterns and uncover the mechanisms underlying the observed relationships. The primary aim of the first phase of this study is to conduct a cross-sectional investigation into the levels of happiness among nurses working in hospitals. This quantitative approach will involve the administration of standardized surveys to assess various dimensions of happiness, including emotional, social, and cognitive components. By collecting data from a diverse sample of nurses across different hospital settings, the study seeks to quantify happiness levels and identify factors that contribute to or hinder happiness in the workplace. The findings will provide a comprehensive overview of the current state of happiness among nurses, highlighting areas that require attention and intervention. To achieve this aim, the following research hypotheses will be tested:

There is a significant relationship between demographic variables (age, gender, marital status, family income) and nurses’ happiness scores.There is a significant relationship between occupational variables (work experience, employment status, salary satisfaction, overtime hours, shift work) and happiness scores.Nurses who participate in recreational and cultural activities (either at the workplace or outside of it) have higher happiness scores compared to nurses who do not participate in such activities.Satisfaction with physical and mental health has a significant positive correlation with nurses’ happiness scores.A regression model encompassing demographic and occupational variables will be able to significantly predict a portion of the variance in nurses’ happiness scores.

#### 2.1.1 Study setting.

The research will be conducted in hospitals affiliated with Mazandaran University of Medical Sciences. This setting is chosen to ensure a representative sample of nurses working in various clinical environments.

#### 2.1.2 Participants.

The target population for this study consists of nurses employed in hospitals affiliated with Mazandaran University of Medical Sciences.

#### 2.1.3 Inclusion criteria.

Participants must meet the following criteria:

a) Male and female nurses from each unit.b) A minimum of 24 working hours per week.c) At least three years of work experience in nursing.

#### 2.1.4 Exclusion criteria.

Participants will be excluded if they:

a) Express unwillingness to cooperate during the survey process.

#### 2.1.5 Data collection.

Data will be collected using the following instruments:

A. self-design checklist including demographic characteristics and occupational features.B. The standard Oxford Happiness Questionnaire, which will be sent to participants online.

**A. Checklist of demographic characteristics and occupational features:** This checklist will include demographic characteristics and occupational features.

The demographic section will cover: Age, Gender, Number of children, Marital status, Educational background, Spouse’s employment status, Type of housing, Family income, Engagement in recreational or cultural activities, Satisfaction with physical health, Satisfaction with mental health.

The occupational features section will include: Official position of nurses, Employment status, Current department of the workplace, Level of interest in nursing at present, Satisfaction with salary, Number of overtime hours, Shift work, Engagement in recreational activities at the workplace.

**B. Oxford Happiness Questionnaire:** The Oxford Happiness Questionnaire consists of 29 items divided into six subscales: self-esteem, life satisfaction, efficiency, positive mood, sense of control, and mental health. Respondents will answer items on a six-point Likert scale ranging from “strongly disagree” to “strongly agree.” The scoring for the six scales ranges from 1 to 6, leading to a total score that ranges from 29 to 174. A higher score indicates greater happiness. The total score will be classified into three levels: less than 100 indicates low happiness, scores between 101–131 indicate medium happiness, and scores above 132 indicate high happiness [24,25]. The validity and reliability of the Persian version of the questionnaire have been confirmed in previous studies, with a reported Cronbach’s alpha of over 0.90 [24–26].

#### 2.1.6 Sample size.

The initial sample size was calculated using the formula for estimating a population mean: n=(Zα/2 × σ/d)2n=(Zα/2 × σ/d)2. Based on a previous similar study [27], the mean happiness score was 67.43 with a standard deviation (SD) of 17.28. Assuming a 95% confidence level (Zα/2 = 1.96Zα/2 = 1.96) and a margin of error (d) of 2 points, the calculated sample size was 287. However, to account for the two‑stage cluster sampling design where hospitals are first randomly selected, followed by the random selection of nurses within each hospital proportionate to the hospital’s nursing staff size a design effect (DE) will be incorporated into the sample size calculation. The design effect is computed using the formula DE = 1 + (m − 1) × ICC, where m represents the average cluster size (the number of participants per hospital) and ICC denotes the intra‑cluster correlation coefficient. Based on previous similar studies conducted in Iran examining health outcomes among healthcare workers, an ICC of 0.05 is assumed for happiness‑related variables among nurses within the same hospital. With an estimated average cluster size of 34 nurses per hospital (derived by dividing the total target sample by the number of hospitals), the design effect is calculated as 1 + (34 − 1) × 0.05 = 2.65.

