#### 2.1.7 Randomization.

Sampling in the quantitative phase will be conducted in two stages. In the first stage, a list of all hospitals in the province (26 hospitals) will be prepared through Mazandaran University of Medical Sciences, from which 10 hospitals will be randomly selected. The names of the hospitals will be written on cards, placed in a box, mixed, and then 10 cards will be drawn one by one. In the second stage, participants will be selected from each hospital using random sampling based on the number of nurses employed in each facility. Each hospital will provide a list of nurses’ IDs to the study coordinator, who will code these identifiers and create a master list. The required number of samples will then be selected from this list using a random number table, after which the selected individuals will be contacted to assess their eligibility and willingness to participate.

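### The design effect of 2.65 uses the equal-cluster formula although nurses are allocated in proportion to hospital staff, so without a finite-population correction it is too low whenever hospitals differ in size

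*Protocol article*

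**What the plan says.** Section 2.1.6 starts from a simple random sample. It takes a previous study in which "the mean happiness score was 67.43 with a standard deviation (SD) of 17.28" and, with "a margin of error (d) of 2 points, the calculated sample size was 287". It then says that a design effect will be brought in for the two-stage design, in which hospitals are drawn first, "followed by the random selection of nurses within each hospital proportionate to the" hospital's nursing staff. The formula is DE = 1 + (m − 1) × ICC, "where m represents the average cluster size (the number of participants per hospital"). For the inputs, "an ICC of 0.05 is assumed for happiness"-related variables, and m is an "average cluster size of 34 nurses per hospital (derived by dividing the total target sample by the number of hospitals"). The result is 2.65. The section ends there, with no inflated sample size and no margin under clustering.

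Section 2.1.7 describes the same allocation: "participants will be selected from each hospital using random sampling based on the number of nurses employed in each facility". It also shows that the 10 hospitals are picked from 26 by drawing cards from a box, so each hospital has the same chance of selection whatever its size. Section 2.1.8 plans linear mixed models with a random intercept for hospital.

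**The concern.** The formula and the sampling scheme do not match. With a plain average for m, the formula describes clusters of equal size. Equal clusters would arise if, for example, hospitals were drawn with probability proportional to size and each gave a fixed number of nurses. The article does the reverse: an equal-probability draw, then a number of nurses that rises with hospital staff. Large hospitals then carry more of the sample, and each extra nurse from a hospital already heavily sampled adds less information.

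At stake is the figure meant to inflate the sample size. If 2.65 is carried forward, the final number of nurses, or the precision claimed for the mean happiness score, will be somewhat too favourable. The bias has one direction within the article's framework, and a revision that keeps the equal-cluster formula would carry it into the new figure.

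**Working it through.** **Inputs from section 2.1.6:** Z = 1.96, SD = 17.28, d = 2, ICC = 0.05, m = 34. **From 2.1.7:** 10 of 26 hospitals, equal-probability draw, allocation by staff size. **Not in the document:** hospital staff counts or their variation. CV is therefore an assumption, shown as a range.

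**Step 1. Reproduce the stated figures.** n = (1.96 × 17.28 / 2)² = 286.77, rounded up to 287. DE = 1 + 33 × 0.05 = 2.65. Both agree with the article.

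**Step 2. Equally weighted mean with unequal clusters.** The average m is replaced by the size-weighted average m(1 + CV²):

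DE = 1 + ((1 + CV²) × 34 − 1) × 0.05 = 2.65 + 1.70 × CV².

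The excess is positive for every CV above 0.

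**Step 3. Random-intercept model.** This estimator gives large hospitals less weight, so the loss is smaller. A second-order approximation is DE = 2.65 / (1 − CV² × L × (1 − L)), with L = 1.70 / 2.65 = 0.64.

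**Step 4. First-stage finite-population correction.** If only the 26 listed hospitals are the target, the between-hospital part is multiplied by 16/26: DE = 0.95 + 1.70 × (1 + CV²) × 16/26 (equally weighted mean).

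| CV (assumed) | DE, equally weighted | DE, random intercept | DE, equally weighted with 16/26 correction |
|---|---|---|---|
| 0 | 2.65 | 2.65 | 2.00 |
| 0.3 | 2.80 (+6%) | 2.71 (+2%) | 2.09 |
| 0.5 | 3.08 (+16%) | 2.81 (+6%) | 2.26 |
| 0.7 | 3.48 (+31%) | 2.99 (+13%) | 2.51 |

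The last column passes 2.65 when (1 + CV²) × 16/26 = 1, that is CV² = 0.625, or CV of about 0.79.

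**Step 5. A concrete allocation, for illustration only.** Samples of 10, 15, 20, 25, 30, 35, 40, 45, 55 and 65 total 340, with mean 34 and CV 0.49. The sum of squares is 14,350, so the size-weighted cluster size is 14,350 / 340 = 42.2 and DE = 1 + 41.2 × 0.05 = 3.06. With random-intercept weights, DE = Σmᵢ / Σ[mᵢ / (1 + (mᵢ − 1) × 0.05)] = 2.82.

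**Step 6. What this does to a margin.** The article gives no clustered margin. Taking the 340 nurses implied by 34 × 10, the margin is 1.96 × 17.28 × √(DE/340). It is ±2.99 at DE 2.65. At CV 0.3, 0.5 and 0.7 it is ±3.08, ±3.22 and ±3.43 for the equally weighted mean, and about ±3.02, ±3.08 and ±3.17 under the random-intercept model. None of these uses a finite-population correction.

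**Step 7. The value of m.** Multiplying through, 287 × 2.65 = 760.55, or 761 nurses. That is about 76 per hospital, not 34. At about 76 per hospital, even the equal-cluster formula gives about 1 + 75 × 0.05 = 4.75. A CV term added at m = 34 would still leave a design effect that does not belong to the inflated sample.

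**The case against.** - **There is no slip in the arithmetic.** This stands. The article defines m openly as an average and 2.65 follows. The fault is that the formula does not fit the design.
- **A finite-population correction could more than offset the term.** Ten of 26 hospitals are drawn without replacement, and section 2.1.2 defines the target as nurses in the university's affiliated hospitals. If the 26 are the whole target, 2.65 is conservative at each CV in the table. This limits the claim. It does not justify the formula, because the article neither applies nor mentions such a correction.
- **CV is unknown, and the planned model softens the loss.** Both stand. At CV 0.5 and 340 nurses, the random-intercept margin widens by less than 0.1 point on a scale from 29 to 174. Moving the assumed ICC from 0.05 to 0.06 would do more (1 + 33 × 0.06 = 2.98).
- **The hypotheses in section 2.1 mostly concern associations.** This also stands: a design effect for an overall mean does not directly set their precision. It does bear on the happiness level, which the sample size was built to estimate.
- **Other faults in the same section are larger.** This is true. The 2.65 is never multiplied through and m does not agree with the result. With 10 equal clusters, ICC 0.05 and no correction, the margin cannot fall below 1.96 × 17.28 × √(0.05/10) = 2.39 points, so 2 points is out of reach at any number of nurses. Mending the CV term alone would not repair the calculation.

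A reader might also infer that the article gives unequal hospital size as its reason for proportional allocation. It gives no reason. Unequal size is a fair inference, since such allocation would otherwise have no effect.

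**Conclusion.** The point holds with conditions. Under ICC 0.05, m = 34 and no finite-population correction, 2.65 is too low for the sampling scheme in sections 2.1.6 and 2.1.7 whenever hospitals differ in size. The direction is certain in that framework; the size is not, because it rests on an assumed CV. For CV between 0.3 and 0.7 the excess is about 6% to 31% for an equally weighted mean and about 2% to 13% under the planned model.

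Two stronger readings are not supported. The first is that 2.65 understates the design effect whatever the target: with inference confined to the 26 hospitals and the correction applied, that is so only above a CV of about 0.79. The second is that a stated precision under clustering is wrong: the article states none, and the margins above are derived here from an implied total of 340. The matter is secondary to completing the design-effect calculation.

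**What to change.** Make this change when the calculation in section 2.1.6 is completed:

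1. Obtain nurse counts for the listed hospitals and compute the CV of the planned per-hospital samples.
2. Say whether inference is to the 26 listed hospitals or beyond them, and hence whether a first-stage finite-population correction applies.
3. Recompute the design effect with 1 + ((1 + CV²) × m − 1) × ICC, or its mixed-model equivalent, using an m that agrees with the final total. Because m and the total depend on each other, they must be solved together.
4. State the design effect and the expected margin for the number of nurses actually planned.

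The article says recruitment has not begun, so the counts can be used in time. The work is a request for counts, a recalculation and a few sentences. The downside is that the stated precision will look somewhat less favourable, unless the target is restricted to the 26 hospitals and the correction applied.

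### A design effect of 2.65 is computed but never applied, the cluster size of 34 matches no stated total, and ten hospitals do not deliver ±2 points at any sample size the protocol implies

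*Protocol article*

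**What the plan says.** Section 2.1.6 uses the formula for estimating a mean. Its inputs are a prior study in which "the mean happiness score was 67.43 with a standard deviation (SD) of 17.28", a 95% confidence level, "and a margin of error (d) of 2 points, the calculated sample size was 287". The section calls 287 the initial sample size. It then turns to the two-stage design and says that "a design effect (DE) will be incorporated into the sample size calculation", using DE = 1 + (m − 1) × ICC with an assumed ICC of 0.05. The cluster size is introduced so: "With an estimated average cluster size of 34 nurses per hospital (derived by dividing the total target sample by the number of hospitals". The result is 2.65, and the section ends there.

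Section 2.1.7 fixes the number of clusters. A list of 26 hospitals is drawn up, "from which 10 hospitals will be randomly selected". The required number of nurses is then drawn from each hospital's list, "after which the selected individuals will be contacted to assess their eligibility and willingness to participate". The article gives no total other than 287.

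Section 2.1.8 plans linear mixed models with hospital as a random intercept, and says that the ICC will be calculated.

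**The concern.** The calculation is set out step by step, but its last step is absent. A reader cannot tell whether the survey is to recruit 287, 340, 761 or some other number, although section 2.1.7 relies on a required number of samples.

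The cluster size is also circular. It is said to come from the total target sample, but no stated total divided by ten gives 34.

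The quick repair, multiplying 287 by 2.65, fails as well. With the number of hospitals fixed at ten, more nurses means more nurses per hospital, and the design effect rises with them.

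Quantifying nurses' happiness is the primary aim of this phase (section 2.1), and ±2 points is the only precision target in the article. The number of hospitals is the binding constraint and is hard to change once the ten are drawn. The methods section says that recruitment has not started, so the plan can still be corrected cheaply.

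**Working it through.** **Inputs.** SD 17.28, z = 1.96, d = 2, ICC 0.05 and m = 34 (section 2.1.6); 10 of 26 hospitals (section 2.1.7).

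**1. The plan's own figures reproduce.**
- n = (1.96 × 17.28 / 2)² = 286.8, rounded up to 287.
- DE = 1 + 33 × 0.05 = 2.65.

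**2. The cluster size does not fit.**
- 34 × 10 = 340, which is not stated.
- 287 / 10 = 28.7, for which DE = 1 + 27.7 × 0.05 = 2.385.
- 287 × 2.65 = 760.6, so 761, or 76.1 per hospital. Then DE = 1 + 75.1 × 0.05 = 4.755.
- 761 nurses at 34 per hospital would need 761 / 34 = 22.4 hospitals, so 23, not ten.

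**3. The loop does not close with ten hospitals.** With m = n/10, DE = 0.95 + 0.005n. Requiring n = 287 × DE gives n = 272.65 + 1.435n. Because 1.435 exceeds 1, there is no positive solution. Repeated substitution from 287 diverges: 685, 1,255, 2,073 and so on.

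**4. Margin delivered.** The half-width is z × SD × √(DE/n). With ten hospitals this equals 1.96 × 17.28 × √(0.05/10 + 0.95/n). The last two columns add a first-stage finite-population correction, multiplying 0.05/10 by 1 − 10/26 = 16/26. The last column also uses t on 9 degrees of freedom in place of z.

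| n | per hospital | DE | z, as in the protocol | z, with 10/26 correction | t (9 df), with 10/26 correction |
|---|---|---|---|---|---|
| 287 | 28.7 | 2.385 | ±3.09 | ±2.71 | ±3.12 |
| 340 | 34 | 2.65 | ±2.99 | ±2.60 | ±3.00 |
| 761 | 76.1 | 4.755 | ±2.68 | ±2.23 | ±2.57 |
| no limit | – | – | ±2.39 | ±1.88 | ±2.17 |

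At n = 340 the effective sample size is 340 / 2.65 = 128.

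**5. When ±2 would be reached.** The variance ratio needed is (2 / 33.87)² = 0.003487, where 33.87 = 1.96 × 17.28.
- Ten hospitals, with correction and z: n = 0.95 / (0.003487 − 0.005 × 16/26) = about 2,316 nurses.
- Ten hospitals, no correction: ICC/10 must lie below 0.003487, so the ICC must be below about 0.035. The n needed is about 398 at ICC 0.01, 659 at 0.02 and 1,992 at 0.03.
- ICC 0.05, no correction: at least 0.05 / 0.003487 = 14.3, so 15 hospitals.

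**The case against.** Four points can be made for the plan.

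**±2 is not strictly out of reach.** A reader might infer that ten hospitals can never give ±2. The documents do not support that without conditions. Ten of 26 hospitals is a large first-stage fraction, and with that correction and z, ±2 is formally reachable at about 2,316 nurses. It is also reachable without the correction if the ICC is below about 0.035. This stands as a limit on the wording. It does not rescue the plan, because the protocol mentions no such correction, assumes an ICC of 0.05, and implies no size near 2,316.

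**The survey would not report a false ±2.** A reader might infer that results will be published with a margin of ±2 when the real one is about ±3. That does not follow. ±2 is a planning input, and section 2.1.8 models hospital as a random intercept, so the reported intervals should reflect the clustering. This stands. The harm lies in planning, not in reporting.

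**The 34 may contain a non-response allowance.** With 15% non-response, 287 / 0.85 = 338, close to 34 per hospital. For the same reason, one cannot infer from the eligibility check after the draw that losses were ignored. An allowance may exist in the full protocol, and an article may leave it out. But section 2.1.6 gives a different origin for 34, and a factor of 340 / 287 = 1.18 is not a design effect of 2.65.

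**The article is a condensed text.** That would excuse a missing detail. It does not excuse a cluster size that contradicts the stated totals.

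**Conclusion.** The point holds. The design effect is computed but not applied, and the only stated total assumes simple random sampling. The cluster size of 34 agrees neither with that total nor with its inflated value. With ten hospitals the planned ±2 is missed at each size the protocol implies: by about half at 287 and 340 (±3.09 and ±2.99) and by about a third at 761 (±2.68).

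These figures rest on the protocol's own SD of 17.28, its ICC of 0.05, equal cluster sizes and the number of completed responses shown. With the 10/26 correction the margins narrow to between ±2.23 and ±2.71 with z, which still misses ±2.

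**What to change.** **Main change, in section 2.1.6.** State one final n, and one m that equals that n divided by ten. Replace ±2 with the margin that this n delivers. If 340 is the intended total, the text could say: 340 nurses in ten hospitals (m = 34, DE 2.65, effective n 128) give a 95% half-width of about ±3.0. With the 10/26 correction the figure is ±2.6 using z, or ±3.0 using t on 9 degrees of freedom. Say which basis is used. If a non-response allowance lies behind the 34, state it and say whether n counts nurses drawn or responses completed. The cost is a few sentences and a less favourable stated margin.

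**What not to do.** Stating 761 with ten hospitals and keeping ±2 would put a second wrong figure in place of the first.

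**Optional alternative, if ±2 must be kept.** Sample proportionally from all 26 hospitals. With hospital analysed as a stratum, 287 completed responses give 1.96 × 17.28 × √(0.95/287) = ±1.95. This would require section 2.1.8 to change: under the planned random intercept the figure is 1.96 × 17.28 × √(0.05/26 + 0.95/287) = about ±2.45. It also needs staff lists, permissions and written consent at 16 more hospitals, and enough nurses drawn to yield 287 responses.
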